### Statistical Analysis

The sample size was calculated based on the primary endpoint using the exact binomial test. For this trial, we defined feasibility as the ability of ≥80% of trial patients to answer ≥80% of mobile ePROM questions during the course of (chemo)radiation therapy. With an assumed percentage of 89% for the primary endpoint, a sample size of 50 patients in the experimental arm provides a power of 80% (1 – β) to a one-sided significance level of 5% (α). Power calculations were carried out using G*Power software version 3.1.9.2 (University of Düsseldorf, Germany).

Descriptive statistics will be used to analyze the secondary endpoints, including mean (SD) as well as median (IQR) for continuous variables, and absolute and relative numbers for categorical variables. Multivariate regression models will be employed to assess potential correlations between clinical parameters and data collected for the primary and secondary endpoints. The control group will be included in the analysis, and the randomization of each patient will be considered as a variable. Sum scores will be derived from the quality of life and patient satisfaction questionnaires, and will be compared between study arms using Mann-Whitney *U* tests.

To investigate the association between patient-reported outcomes and the necessity for inpatient treatment, a chi-square test will be employed.

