**Results:**

This trial will enroll 100 patients who will be randomized (1:1) between the experimental arm with ePROM monitoring and the control arm with standard patient care. Recruitment will take 18 months, and trial completion is planned at 24 months after enrollment of the last patient.

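### The stated 80% power for the primary endpoint does not follow from its inputs: 50 experimental-arm patients give about 52% power against the 80% feasibility threshold

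*Protocol article*

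**What the plan says.** All of the sample size reasoning is in Methods, Statistical Analysis:

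- Test: "The sample size was calculated based on the primary endpoint using the exact binomial test".
- Success threshold: "we defined feasibility as the ability of ≥80% of trial patients to answer ≥80% of mobile ePROM questions". The Abstract (Methods) gives the same two-level 80% definition.
- Assumed rate, sample size and result: "With an assumed percentage of 89% for the primary endpoint, a sample size of 50 patients in the experimental arm provides a power of 80" per cent, at a one-sided significance level of 5%. G*Power is named as the software.

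The Abstract (Results) gives 100 patients in total, randomised 1:1. Under ePROM Monitoring During Treatment and Support, only the experimental arm uses the app, so only those 50 patients can contribute to the primary endpoint.

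No proportion is labelled as the null hypothesis. The 80% threshold is the only one attached to the primary endpoint. A figure of 75% appears in Limitations and Future Perspectives, as a survey result on patients' willingness to report.

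**The concern.** A gap of 9 percentage points between a threshold of 80% and an assumed rate of 89% is small for a single-group test in 50 patients. At 80% the standard error of the observed proportion is √(0.80 × 0.20 / 50) = 0.057, so the gap is only about 1.6 standard errors (0.09 / 0.057). A one-sided 5% test already needs 1.645 standard errors to reject, so power should be close to one half, not 80%.

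The size of the trial rests on this one calculation. If the power is really about one half, a trial in which the sponsor's own assumption is true would miss its primary endpoint almost as often as it met it, and a workable monitoring system could be reported as not shown feasible. The article also makes the next trial, on patients' own devices, conditional on feasibility having been demonstrated.

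**Working it through.** **Inputs** (Statistical Analysis): n = 50; reference p0 = 0.80, the feasibility threshold; assumed rate p1 = 0.89; one-sided α = 0.05; exact binomial test. Stated result: power 0.80.

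**Step 1: critical value.** Let X be the number of the 50 patients who answer at least 80% of their questions. The test rejects at the smallest r with P(X ≥ r | p0) = Σ C(50,k) 0.80^k 0.20^(50−k), summed over k = r to 50, no larger than 0.05.

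- P(X ≥ 44 | 0.80) = 0.103, too large
- P(X ≥ 45 | 0.80) = 0.048, allowed

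Success therefore requires at least 45/50, an observed 90%.

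**Step 2: power.** P(X ≥ 45 | 0.89) = Σ C(50,k) 0.89^k 0.11^(50−k), k = 45 to 50, which is 0.524. Type II error is 1 − 0.524 = 0.476. The stated 80% is not reproduced; the gap is 80 − 52.4 = 27.6 percentage points.

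**Step 3: could another method give 80% with the same inputs?** All rows use n = 50, rates of 80% and 89%, and one-sided 5% unless noted.

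| Variant | Power |
|---|---|
| Exact binomial | 52.4% |
| Exact binomial, one-sided 2.5% | 34.4% |
| Normal approximation, null variance for the critical value | 47.3% |
| Same, with continuity correction | 38.4% |
| Normal approximation, variance at 89% throughout (Wald) | 65.1% |
| Arcsine transformation | 55.2% |
| Hypotheses reversed (null 89%, alternative 80%) | 55.6% |
| Two groups of 50, 80% against 89% | 34.3% |

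None comes close to 80%.

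**Step 4: what would give about 80%?**

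| Change | Rejection rule | Actual α | Power at 89% |
|---|---|---|---|
| n = 100, reference 80% | ≥87/100 | 0.047 | 79.2% |
| n = 106, reference 80% (first n to reach 80%) | ≥92/106 | 0.047 | 81.4% |
| n = 50, reference 75% | ≥43/50 | 0.045 | 82.1% |

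Exact power moves in steps. With a reference of 80% it stays at or above 80% from n = 118 onward (checked to n = 259). If n = 50 and the 80% reference are both kept, 80% power requires a true rate of about 92.1%; at 92% the power is 79.2%.

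**Step 5: does the 75% reference support the endpoint?** Its rule, at least 43/50, has P(X ≥ 43 | 0.80) = 0.190. If the true rate is exactly at the 80% threshold, the test still succeeds 19% of the time, so it is not a 5% test of the stated threshold.

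**Step 6: losses.** Fewer analysed patients reduce the power further. With 45 analysed, the rule is at least 41/45 and power is 43.9%.

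**The case against.** The strongest objection is that the article never names a null proportion. A feasibility target and the null of a power calculation are different quantities, and single-arm designs often test against a lower, unacceptable rate. A null of 75% fits the design well: with an alternative of 89% and one-sided exact 5%, the first sample size to reach 80% power is exactly 50 (at least 43/50, power 82.1%). Exact power moves in steps, so overshooting 80% at the smallest qualifying n is normal. The 75% also appears in the article, in the survey argument for the threshold. On this view the power was computed correctly and the fault is an unreported null.

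Much of this stands. The 52% is conditional on a null of 80%, and 75% is a plausible origin of the figure. Another is that the total of 100 was entered (79.2%), which fits less well because the text attributes the power to "a sample size of 50 patients in the experimental arm". The article confirms neither. But a 75% null does not rescue the sentence: the test would then show only that more than 75% of patients comply, while feasibility is defined at 80% or more.

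A second objection is that feasibility may simply mean an observed proportion of at least 80%, or 40/50. At a true 89% that is met 98.2% of the time. But the same rule succeeds 58.4% of the time at a true rate of exactly 80%, which contradicts the stated 5% level, and it does not give 80% power either.

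The absence of a separate analysis plan does not settle the matter. The article prints a specific power alongside its inputs, and the two disagree.

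**Conclusion.** The point holds. With 50 patients, a one-sided exact 5% test and the only success threshold the article gives, power at 89% is 52.4%, not 80%, and the type II error is 47.6%, not 20%. The assumption behind this is that the null equals the 80% feasibility threshold and that all 50 experimental-arm patients are analysed. If the null was instead 75%, the power figure is roughly right (82.1%) but belongs to a different and weaker claim. On each reading considered, the stated power does not belong to the stated primary endpoint.

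That the printed figure cannot be reproduced is certain. How it arose cannot be determined from the article. The correction is necessary because the sample size has no other justification.

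**What to change.** First, check the G*Power entry and state the null proportion and the success count. Then use whichever wording applies:

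- **Null 80%:** with n = 50, H0: p ≤ 0.80 and rejection at 45/50 or more, the exact one-sided α is 0.048; power is 52% at a true rate of 89%, 79% at 92%, and 80% at about 92.1%.
- **Null 75%:** state H0: p ≤ 0.75, rejection at 43/50 or more, exact α 0.045 and power 82% at 89%. Reword the feasibility conclusion so that a positive test is read as showing more than 75%, and reconcile this with the 80% definition in the Abstract and in Statistical Analysis.

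Either way, the result should be reported against the stated count so that the decision rule is fixed before the data are seen.

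The cost is a change of wording in the protocol and any analysis plan, with no additional patients. Under the first option the stated power becomes less favourable; under the second the claim becomes weaker. Keeping both the 80% threshold and 80% power at 89% would be a design change, not a rewording: it would need 106 analysed app users in place of 50.

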**Methods:**

This prospective randomized single-center trial will evaluate the feasibility of integrating electronic patient-reported outcome measures (ePROMs) into the treatment workflow of HNC patients. Patients undergoing definitive or adjuvant (chemo)radiation therapy as part of their HNC treatment at the Department of Radiation Oncology, University Medical Center Freiburg (Freiburg, Germany) will receive weekly physician appointments and additional appointments as requested to monitor and potentially treat symptoms during the course of treatment. Patients in the experimental arm will additionally be monitored daily using a dedicated app regarding their disease- and treatment-related symptoms, quality of life, and need for personal physician appointments. The feasibility of ePROM monitoring will be tested as the primary endpoint and will be defined if ≥80% of enrolled patients have answered ≥80% of their daily app-based questions. Quality of life will be assessed using the validated European Organisation for Research and Treatment of Cancer questionnaires, and patient satisfaction will be measured by the validated Patient Satisfaction Questionnaire Short Form at the initiation, in the middle, and at completion of radiation therapy, as well as at follow-up examinations. Additionally, the number and duration of physician appointments during the course of radiation therapy will be quantified for both ePROM-monitored and standard-of-care patients.

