### Primary and Secondary Endpoints

This trial aims to test the feasibility of an ePROM-based treatment monitoring and support system for HNC patients as the primary endpoint. The trial will measure the percentage of patients answering ≥80% of ePROM questionnaires during the course of (chemo)radiation therapy, and the number of answered questions for each treatment day will be documented for every patient to assess feasibility. Feasibility in this trial is defined based on clinical and logistical considerations. We assume that due to logistic constraints unrelated to this trial, patients will not receive ePROM questionnaires for a certain percentage of treatment fractions (eg, due to personnel changes, technical outages, postponement of treatment fractions). Based on clinical experience from preliminary tests, we assume that the proportion of irregularities during routine patient treatment will amount to approximately 20%.

The following secondary endpoints will also be measured: patient satisfaction, health-related quality of life, number and duration of physician appointments, number of days spent as an inpatient for treatment-related toxicities, and cost aspects. Patient satisfaction will be measured by a 10-step visual analog scale and the validated Patient Satisfaction Questionnaire Short Form (PSQ-18) questionnaire that tests 18 items in 7 subscales using a Likert scale ranging from 1 to 5. A total sum score will be calculated from the PSQ-18 questionnaire and will be transformed to a 5-point scale. Health-related quality of life for patients in both study arms will be measured using the validated EORTC QLQ-C30 questionnaire.

Patients will be asked to answer questionnaires before the initiation of (chemo)radiation therapy, in the middle (usually week 4), and upon completion of treatment (Figure 1). Additionally, patients will be presented with the questionnaires at follow-up visits.

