The number of all physician appointments will be documented, and the duration of individual appointments will be measured to estimate cost factors for ePROM monitoring during treatment. The beginning and completion of physician appointments are routinely marked by status flags by the physician within the hospital’s radiation oncology information system (MOSAIQ, Elekta, Stockholm, Sweden), and the duration of each individual consultation can therefore be extracted from the system. A randomized design was chosen for this trial to assess the completeness of acquired data between both arms and to compare the two groups regarding the secondary endpoints.

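### The only between-arm test named for quality of life and satisfaction makes no stated use of the pre-treatment score; a baseline-adjusted difference with confidence interval would be a free gain in precision

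*Protocol article*

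**What the plan says.** Three parts of the Statistical Analysis section bear on these scores.

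- The between-arm test: "Sum scores will be derived from the quality of life and patient satisfaction questionnaires, and will be compared between study arms using Mann-Whitney" U tests. The sentence does not say whether raw or change scores are compared, at which visit, or with what effect measure.
- The summaries: "Descriptive statistics will be used to analyze the secondary endpoints, including mean (SD) as well as median (IQR) for continuous variables".
- The regression: "Multivariate regression models will be employed to assess potential correlations between clinical parameters and data collected for the primary and secondary endpoints". The next sentence brings in the control group and adds that "the randomization of each patient will be considered as a variable".

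On data collection, Primary and Secondary Endpoints says: "Patients will be asked to answer questionnaires before the initiation of (chemo)radiation therapy, in the middle (usually week 4), and upon completion of treatment", with further questionnaires at follow-up visits. The abstract's Methods paragraph confirms this for satisfaction: "patient satisfaction will be measured by the validated Patient Satisfaction Questionnaire Short Form at the initiation, in the middle, and at completion of radiation therapy". It puts the EORTC quality of life questionnaires on the same schedule. So a pre-treatment score is planned for every patient on both instruments.

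The last sentence of Primary and Secondary Endpoints gives two reasons for randomizing. One is to assess completeness of data in the two arms; the other is "to compare the two groups regarding the secondary endpoints".

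**The concern.** When an outcome is measured before and after randomization, the pre-treatment value usually explains part of the spread in later values. A model that includes it estimates the arm difference more precisely from the same patients. A Mann-Whitney test cannot take a covariate, so by naming it as the comparison the protocol gives the collected baseline no role in that comparison. The test also returns a p-value and no difference with an interval.

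The primary endpoint concerns app use in the experimental arm only, so the 50 control patients serve mainly the secondary comparisons. The Conclusions section says the trial should form the basis of larger investigations of clinical benefit. Planning those calls for an estimated difference and its uncertainty more than for a p-value.

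**Working it through.** **No figure of the plan's own to reproduce.** The article states power only for the primary endpoint. It gives no sample size, target difference or power for quality of life or satisfaction.

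**Inputs**
- From the abstract (Results): 100 patients randomized 1:1, so n = 50 per arm.
- Assumed, not in the document: two-sided 5%, 80% power, normally distributed scores, all 50 per arm analysed, and a baseline-to-outcome correlation r from 0.3 to 0.7.

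**Step 1: no baseline.** The detectable difference in SD units is (1.960 + 0.842) × √(2/n).
- Comparison of means: 2.802 × √(2/50) = 2.802 × 0.200 = 0.560.
- Mann-Whitney, with asymptotic relative efficiency 3/π = 0.955 under normality: 0.560 / √0.955 = 0.573.

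**Step 2: with baseline.** Adjustment leaves residual variance 1 − r², so the detectable difference is 0.560 × √(1 − r²). The equivalent unadjusted sample size per arm is 50 / (1 − r²). The approximate power for a true difference of 0.5 SD is Φ(0.5 / (0.200 × √(1 − r²)) − 1.960). For Mann-Whitney the same power formula with 50 × 0.955 per arm gives 0.686.

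| Analysis | Residual variance | Detectable difference (SD) | Equivalent n per arm | Power at 0.5 SD | Simulated power |
|---|---|---|---|---|---|
| Mann-Whitney, raw score | – | 0.573 | – | 0.686 | 0.67 |
| Adjusted, r = 0.3 | 0.91 | 0.535 | 54.9 | 0.746 | 0.73 |
| Adjusted, r = 0.5 | 0.75 | 0.485 | 66.7 | 0.823 | 0.82 |
| Adjusted, r = 0.7 | 0.51 | 0.400 | 98.0 | 0.938 | 0.93 |

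The last column is from 5,000 simulated trials per value of r, with normal data and a true difference of 0.5 SD. It agrees with the formulas.

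The step from 0.573 to 0.560 is the efficiency of a mean comparison over a rank test under normality. Only the part below 0.560 is owed to the baseline.

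**Step 3: a lower correlation.** At r = 0.2 the residual variance is 1 − 0.04 = 0.96 and the detectable difference is 0.560 × √0.96 = 0.549. The gain is then slight.

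**Step 4: if the test were run on change scores.** The text does not exclude this. With equal variances before and after, a change score has variance 2(1 − r) relative to the raw score. Mann-Whitney on change would then detect 0.573 × √(2(1 − r)): 0.678 at r = 0.3, 0.573 at r = 0.5 and 0.444 at r = 0.7. Because 2(1 − r) − (1 − r²) = (1 − r)² ≥ 0, adjustment is never less precise than change. The recommendation therefore does not depend on which reading is right.

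**Step 5: does the regression sentence already cover this?** Its stated aim is to relate clinical parameters to endpoint data. Arm enters as a variable, but the pre-treatment score is not named as a covariate, and the sentence that follows gives the between-arm comparison of these scores to Mann-Whitney.

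**The case against.** The strongest objections, and what stands of each:

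- **A condensed article leaves covariates, visits and intervals to the full protocol or SAP.** This stands for the visit, raw versus change score and missing-data handling, and none of these is raised here as an omission. It does not cover the choice of test, which the article makes itself.
- **The plan does yield effect information.** A reader might infer from the Mann-Whitney sentence that no effect estimate is planned. That is true of the test but not of the plan: means, medians and a regression containing the arm are all foreseen, and the regression could give an arm coefficient. What is missing is a baseline-adjusted difference with an interval, designated as the treatment comparison.
- **Raw post-baseline scores are not stated.** Correct. An unadjusted test of raw scores is the natural reading, not the text.
- **Chance imbalance is not bias.** Correct. Patient Recruitment describes variable-length blocks and does not mention stratification. A reader might infer that chance baseline differences invalidate the comparison, but the test's type I error already allows for them. The argument concerns precision only.
- **Missed visits.** A reader might infer that the rank test discards patients unnecessarily. Applied per visit, it uses everyone observed at that visit, and analysis of covariance per visit does no better and also needs a baseline score. Only a mixed model across visits draws on the incomplete records.
- **The correlation is assumed.** This stands. It may also differ between quality of life and satisfaction, and the efficiency of 0.955 may not hold for skewed or bounded scores.
- **These are secondary endpoints of a feasibility trial, and the comparison is only one of two reasons given for randomizing.** This stands, and it keeps the severity low.

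**Conclusion.** The point holds as a free improvement of low severity. The one named between-arm test makes no stated use of a pre-treatment score collected on both instruments, and no baseline-adjusted difference with confidence interval is named.

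Under the assumptions listed, adjustment lowers the detectable difference from about 0.573 SD to between 0.535 SD (r = 0.3) and 0.400 SD (r = 0.7). For a true 0.5 SD difference, power rises from about 0.69 to between 0.75 and 0.94. The gain is modest at low correlation and substantial from about r = 0.5.

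The documents do not support saying that the planned test is invalid or biased, or that the feasibility conclusion is affected.

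**What to change.** In the Statistical Analysis section and the SAP, replace Mann-Whitney as the main between-arm comparison of the quality of life and satisfaction scores with one of these:

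- analysis of covariance at end of treatment, with arm and baseline score; or
- a repeated-measures mixed model across visits, with arm, visit, arm × visit and baseline score. This is preferable if missed visits are expected.

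Report the adjusted mean difference with 95% CI at end of treatment and, if the mixed model is used, at the other visits. Keep Mann-Whitney as a sensitivity analysis, which also answers doubts about bounded or skewed scores.

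The cost is a change of wording, made before the data are analysed, and a little more analysis work. No extra patients, visits or questionnaires are needed.

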## Methods

### Study Design

This trial is designed as a single-center prospective randomized controlled trial and will be carried out at the Department of Radiation Oncology, University of Freiburg Medical Center in Freiburg, Germany. Patients with histologically proven HNCs scheduled for (chemo)radiation therapy will receive weekly physician appointments and additional appointments if medically indicated in both trial arms to monitor and potentially treat symptoms occurring during the course of treatment (standard of care). Patients in the experimental arm will additionally receive daily ePROM monitoring during (chemo)radiation. Patient-reported outcomes regarding symptom control as well as general and disease-specific quality of life will be monitored daily by a mobile app in the experimental arm that is provided to the patients on a tablet computer. All patients in the experimental arm will have the ability to request a physician appointment if necessary on a daily basis via the app. The frequency and total duration of consultations will be quantified, and the necessity and duration of inpatient care will be assessed if necessary during the course of treatment. Routine blood test results and clinical data from the patient files, including physician-reported outcomes, will be analyzed to find potential correlations with the ePROMs and to assess potential predictive factors necessitating intensified medical care.

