### ePROM Monitoring During Treatment and Support

Patients that are randomized to the experimental arm will be provided with a mobile app on a tablet computer prior to each radiation treatment fraction and will be asked to answer 7-8 questions. The app will be provided by ONCARE GmbH (Munich, Germany) and will be run on an Android system. An introductory session with a study nurse will be scheduled for each patient in the experimental arm to familiarize them with the tablet and the app. If requested, this introductory session can be repeated once. The answers will be collected and documented as patient-reported outcomes. Questions will be taken from the validated H&N35 quality of life questionnaire developed by the European Organisation for Research and Treatment of Cancer (EORTC). The questions cover overall and treatment-related well-being as well as specific symptoms, and the 35 questions of the EORTC module will be rotated so that each patient is presented with each question once weekly. As the respective questionnaires have been validated in multiple languages, the monitoring app will be multilingual. After completing the daily EORTC questions, patients will be asked about their need to consult a physician on each treatment day. If they require a physician appointment, the radiation technologist is informed by an automatic notification system prior to applying the daily treatment and will schedule a consultation with the treating physician on that day. Each patient in the experimental study arm will be seen by the treating physician for routine checkups weekly in addition to the visits requested through the app. The total number and duration of all physician appointments will be measured and documented.

Patients in the standard-of-care arm will receive routine weekly physician appointments during the course of treatment and can request additional consultations through the treating radiation technologist as per institutional standards. Patients in both study arms will also receive weekly blood tests. As the standard-of-care physician appointments are also part of the experimental arm, the mobile therapy monitoring provides an additional individualized method of care during (chemo)radiation therapy.

A sample screenshot of the mobile app is shown in Figure 2.

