### Conclusions

The present trial aims to demonstrate the feasibility of ePROM monitoring of HNC patients during (chemo)radiation therapy. The planned secondary endpoints of this study will provide useful data regarding patterns of symptoms during therapy that may predict inferior outcomes or the occurrence of higher-grade treatment-related toxicities. In this respect, this trial will form the basis of future, larger investigations that will assess the potential clinical benefits of app-based monitoring for HNC patients.

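### The chi-square test of patient-reported outcomes against inpatient treatment discards the order of the scores and does not exclude reports made after admission

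*Protocol article*

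**What the plan says.** The Statistical Analysis section names one method for this question: "To investigate the association between patient-reported outcomes and the necessity for inpatient treatment, a chi-square test will be employed". It gives no unit of analysis, categories or reporting window.

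Other sections describe the data that would enter the test:

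- App data, experimental arm only (ePROM Monitoring During Treatment and Support): "the 35 questions of the EORTC module will be rotated so that each patient is presented with each question once weekly".
- Questionnaires, both arms (Primary and Secondary Endpoints): "Patients will be asked to answer questionnaires before the initiation of (chemo)radiation therapy, in the middle (usually week 4), and upon completion of treatment", and again at follow-up visits.
- Scoring (Statistical Analysis): "Sum scores will be derived from the quality of life and patient satisfaction questionnaires, and will be compared between study arms using Mann-Whitney" U tests.
- The inpatient endpoint (Primary and Secondary Endpoints): "number of days spent as an inpatient for treatment-related toxicities".

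On purpose, Study Design says that routine clinical data will be related to the patient reports and used "to assess potential predictive factors necessitating intensified medical care". The Conclusions expect the secondary endpoints to show "patterns of symptoms during therapy that may predict inferior outcomes or the occurrence of higher-grade treatment-related toxicities". Limitations and Future Perspectives adds that the data could later help to define cut-offs and high-risk symptom patterns that call for intervention.

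**The concern.** A chi-square test treats its categories as unordered and needs one independent observation per patient. The reports are ordered and come several times per patient. To use the test, someone must choose a value or a summary for each patient and, for a sum score, cut it into groups. The cut loses information in a small sample.

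The test also has no time element. If the aim is to find reports that signal a coming need for care, only reports made before the admission are informative. Reports made during or after a stay may be worse because of what led to the stay or what happened in it. Mixed in, they can produce an association where earlier reports carried no signal. The article wants these data to inform later trials, so a spurious predictor could be carried forward.

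**Working it through.** **No figure to reproduce.** The article gives no power, effect size or admission rate for this analysis. Its only power statement concerns the primary endpoint and has no bearing here.

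**Passages side by side.**

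1. The Mann-Whitney sentence treats sum scores as ordered. The chi-square sentence, later in the same section, would need categories if those scores were used.
2. The outcome recorded is a number of inpatient days, whereas the test refers to necessity. A yes/no outcome is therefore implied, and the patient report is the other margin of the table.
3. Of the questionnaire times, only the one before treatment must precede every admission during treatment. The mid-treatment one may fall on either side, and the completion and follow-up ones come after most or all such admissions. App reports continue through the whole course.
4. The regression sentence, "Multivariate regression models will be employed to assess potential correlations between clinical parameters and data collected for the primary and secondary endpoints", does not deal with the order of report and admission.

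**Illustration by simulation.** All inputs are assumptions:

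- 50 patients, the size of the experimental arm, which alone has app data.
- Seven weekly scores, in line with a midpoint at about week 4.
- Score = patient effect (SD 1) + weekly residual (SD 1).
- Admission probability 20, 30 or 40% at an average patient effect, that is, roughly 50 × 0.2 = 10 to 50 × 0.4 = 20 admissions, at a random week from week 2 on.
- Two-sided 5%, uncorrected chi-square on a median split, 3,000 runs per setting. The simulation error is at most 1.96 × √(0.25/3000) = 1.8 points.

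Percentage of runs that reject, at 20 / 30 / 40%:

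| Scenario | Chi-square, mean of all weeks | Rank test, mean of all weeks | Chi-square, week 1 only |
|---|---|---|---|
| No association, no shift | 5.0 / 5.4 / 5.8 | 4.9 / 5.1 / 4.4 | 5.5 / 5.2 / 6.0 |
| True log-odds 0.9 per SD, no shift | 44.3 / 52.2 / 59.6 | 58.2 / 67.5 / 71.5 | 27.5 / 31.3 / 37.3 |
| No association before admission, scores 1 SD worse from admission on | 17.4 / 21.9 / 25.4 | 22.5 / 29.4 / 31.6 | 5.7 / 5.5 / 5.8 |

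- Cost of the cut (row 2, rank test minus chi-square on all weeks): 58.2 − 44.3 = 13.9, 67.5 − 52.2 = 15.3 and 71.5 − 59.6 = 11.9 points.
- Cost of mixing in later reports (row 3): 17 to 25% against a nominal 5%, which is about 3.5 to 5 times as many false positives. With week-1 reports only, the rate stays at about 5 to 6%.
- A rank test alone does not cure the timing problem: on pooled reports it rejects even more often (22.5 to 31.6%). The score must also come from before admission.
- One early score is noisier than an average over the course. In row 2 the week-1 chi-square has lower power than the all-weeks one. A rank test on the week-1 score was not simulated.

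**The case against.** The strongest reply is that the article is a condensed text. Windows, cut-offs and the unit of analysis belong in the full protocol or SAP, and a chi-square test can be confined to baseline or early reports. That is right, and it limits the point to the test that the article names. Whatever detail is added elsewhere, a chi-square test still ignores order and still needs categories.

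A reader might go further in several ways that the text does not support:

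- *That the plan will use post-admission reports or a cut-off chosen from the data.* It says neither. The remark on thresholds in Limitations and Future Perspectives describes later use of the data, not this test.
- *That every use of the test requires cutting.* A single item at one time point is already categorical; there the test is valid and only loses the order.
- *That later reports would reverse the association.* They can create a spurious one; nothing shows a change of sign.
- *That this test is declared a prediction analysis.* The sentence speaks of association. The predictive aims stand elsewhere: Study Design refers to blood results and clinical data alongside the reports, and the Conclusions refer to outcomes and toxicities, not to inpatient care. They make timing relevant but do not define this test.
- *That a time-updated survival model is required.* With about 50 patients and an unknown number of admissions, it may be unstable.

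The simulation inputs are also open to challenge: the article plans no median split and gives no admission rate or size of worsening.

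**Conclusion.** The point holds as a weakness in a stated method. The chi-square test does not fit ordered, repeated reports, and nothing in the article confines it to reports made before admission, although the wider aims need that order in time.

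The size is illustrative: about 12 to 15 points of power lost to a median split, and 17 to 25% false positives if post-admission reports that are 1 SD worse are pooled. Both depend on the assumed inputs above. The second also requires that such reports are in fact used, which the article leaves open. With the QLQ-C30, collected in both arms, up to 100 patients would be available and the figures would differ.

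Severity is minor. The analysis is exploratory and affects neither the primary endpoint nor the comparison of the arms.

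**What to change.** Replace the chi-square sentence with an analysis of this form:

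- **Outcome:** admission for treatment-related toxicity, yes or no.
- **Predictor:** one uncut score per patient, taken before any admission and named in advance. For the QLQ-C30 this can be the baseline score. For app data it can be the score from a fixed early week, once a full rotation of the items is complete, among patients not yet admitted, counting only later admissions.
- **Method:** a Mann-Whitney test of the score by admission status, or a logistic regression with that score as the only covariate, reporting the odds ratio with its 95% CI.
- **Optional extension:** a weekly discrete-time model or a Cox model with the score updated over time, if the number of admissions allows.

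Patient procedures do not change. The cost is a change of wording and slightly more analysis work. The article mentions the need for, duration of and days in inpatient care but does not state that admission dates are recorded, so these would have to be extracted from the patient files. Patients admitted before the chosen week drop out of the app analysis, and a single early score gives up some precision against an average over the course.
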